### Measures for testing hypotheses

The following measures are collected at child ages 12, 24, and 36 months. In addition, the Parent Attitudes and Knowledge Inventory and a family demographics and resources measures were administered at enrollment prior to neonatal age 2 weeks. The parent-report instruments were translated into the appropriate language and are always administered in a standardized structured interview to address significant literacy variation among the parent participants. All instruments are administered by blinded evaluators, who were trained in annual workshops and monitored for quality throughout.

#### Bayley Scales of Infant Development

The Bayley Scales of Infant Development II (BSID) [24] measures both the primary outcome variable, cognitive development in the form of the MDI, and a secondary outcome variable, physical development in the form of the PDI. The BSID is a well-validated measure of development in the first 3.5 years and is commonly used to evaluate EDI programs in high-income countries. However it is not routinely used in L/LMIC. Therefore, extensive testing, some cultural adaptation, thorough training on three occasions throughout the trial, and ongoing monitoring of the evaluators is central to the study. The evaluators administer the BSID directly to each child in the appropriate language using standard material prescribed in the manual.

#### Ages & Stages Questionnaire

The Ages and Stages Questionnaire, 2^nd ^ed. (ASQ) [52] is a 30-item instrument addressing parent-reported child development in the domains of communication, gross motor, fine motor, problem solving, and personal-social development using age-specific forms. It is used in BRAIN-HIT to provide a secondary measure of general child development observed in the home environment. To reduce the impact of variation in literacy, ASQ is administered in an interview format with the parent, who is instructed to report on the child's behavior observed in the home or community. As such, the ASQ complements the information on cognitive development obtained through direct testing with the BSID. The ASQ has been widely used for the assessment of early development, including in numerous L/LMICs [e.g., [53,54]].

#### Ages & Stages Questionnaire: Social-Emotional

The Ages and Stages Questionnaire: Social and Emotional (ASQ:SE) [55] uses between 22-30 items (depending on age) to assess parent-reported child social and emotional functioning in the areas of self-regulation, compliance, communication, adaptive functioning, autonomy, affect, and interaction with people. It is used to measure social-emotional development, a secondary outcome in this research. Except for the specific content, the ASQ:SE is formatted and used in the same manner as the ASQ.

#### Parent Attitudes and Knowledge Inventory

Parent attitudes regarding developmental expectations, contributions towards development, and efficacy in the parenting role are measured with 16 items adapted from other longer and more detailed parent attitude instruments [56-58]. Parent knowledge about early child development is measured with another 16 items adapted from the Knowledge of Infant Development Inventory [59], a 75-item instrument designed to assess parents' factual knowledge of parental practices, child developmental processes, and infant norms of behavior.

#### Child health

The primary health measures are weight, height, and head circumference; screened vision and hearing impairment and severe malnutrition; and immunization status. Additional indicators of health to be determined will be collected at ages 24 and 36 months.

#### Family demographics and resources

Family demographics and economic resources are measured with a modified World Bank tool addressing maternal age, race, and education; family size and assets; and household utilities. In addition, maternal psychosocial resources are measured with 12 items developed for this project to address frequency of her interactions with family members and other women as well as time to manage her life and demands.

#### Intervention dose

The parent trainers maintain detailed records on each home visit made, including date, duration, activities addressed, and reason for missing (if applicable), from which various dose-relevant measures will be calculated. The primary indicator of intervention dose will be number of home visits made per 12-month period.

### Data management

Data from forms completed by evaluators or parent trainers are entered locally into a digital database with range and consistency checks. These data are periodically transmitted electronically to the data coordinating center (DCC; RTI International, Research Triangle Park, NC, USA) where additional data edits, including inter- and intra-form consistency checks, are performed. Descriptive statistics are generated and reported to investigators on a monthly basis to monitor enrollment and retention, completion of home visits, and rescheduled or missed visits, and completion of 12, 24 and 36 month evaluations. Additionally, the study sites receive regular edit reports and reconcile any missing, incomplete, or inconsistent data.

### Data analysis

The primary outcome for the study will be analyzed using an intent-to-treat strategy, where data for all participants who meet the inclusion/exclusion criteria will be included in the analysis, regardless of how many home visits are completed. Secondary analyses will be conducted to evaluate the impact of the adherence to the study protocol (e.g., number of visits) on the relationship of the intervention to study outcomes. Because of high post-neonatal childhood mortality (5%), particularly in the group with asphyxia, some attrition is expected.

Comparisons of MDI between the two trial conditions at the end of the study will employ student's t-test, which are repeated for the birth asphyxia and health comparison groups. Descriptive statistics will be reported as frequencies and percentages for categorical variables and means, standard deviations, and minimum and maximum values for continuous variables. Additionally, generalizing estimating equations models and hierarchical linear modeling will be used to perform the analysis on the primary and secondary outcome variables. Other secondary data analyses involving continuous outcomes will be performed using multivariate analysis. Simple ordinary regression models for continuous models will be used to analyze within treatment group differences in outcomes.

To determine cost-effectiveness, the incremental cost of sustaining a home-based early intervention program will be compared to the "willingness to pay" for a disability-adjusted life year (DALY). Maintenance of a home-based intervention program has a relatively low incremental cost from a programmatic standpoint. The incremental cost per year once the program is established will be the salary of a full time trainer, training equipment, transportation, and supplies. For example, experimental research in Lusaka, Zambia has shown that if the rate of MDI <70 due to birth asphyxia is reduced from 7 to 3.5%, the incremental cost will be around $8.50 per DALY ($22,000 ÷ [3.5/100 absolute risk reduction × 2000 survivors of asphyxia enrolled per year × 37 years life expectancy]). This cost compares favorably with that of other medical procedures [60].

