### Randomization

The data center generated randomization lists for infants with and without birth asphyxia, using a block randomization procedure (randomization occurred within blocks of 4 or 8). Each site was provided with sealed envelopes with the randomization assignment. For each randomized infant with birth asphyxia, the sites then randomized the next one to two infants without birth asphyxia so that an overall ratio of approximately 1-to-2 was achieved.

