#### Staff, training, and implementation

Each site selected EDI trainers and supervisors with appropriate backgrounds to its context, such as education, nursing, public health, and physiotherapy. The trainers conducting the EDI home visits and the supervisors initially participated in a five-day workshop conducted at each research site by experienced EDI professionals from the U.S.. The training covered expectations, rationale, early child development, home visiting procedures, the *Partners for Learning *curriculum and materials, assessment and monitoring of progress, and partnering with parents. Also the Portage Model of home visiting [48] was stressed as a way for the EDI trainers to structure their approach to working with mothers (and other family members) during each visit. The training included practice and feedback. A second workshop was conducted at each site when participating children began to reach age 18 months. While some of the same material was reviewed as at the first workshop, this workshop focused on adapting EDI procedures for the children as they develop and observing trainers in actual home visits, to provide constructive feedback.

Each parent-child pair has an assigned trainer conducting the home visits, which are scheduled to occur every two weeks. A form is used to record each visit and which activities were addressed. One to two activities are taught to the parent at each visit. The trainer demonstrates the activity with the child and explains its value. The parent then practices the activity with the child and is given encouraging feedback to fine-tune her interaction with the child. The parent is given the card demonstrating each activity that has been addressed in the visit and is instructed to apply the activities as frequently as possible in her everyday interactions with the child until the next visit.

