### Power analysis

The primary hypothesis is that a home-based EDI plus HSC compared to HSC alone will improve the BSID MDI at 36 months by 10 points in children with birth asphyxia. At least 40 participants per condition who complete the 36 month assessment in each randomization group (birth asphyxia and healthy comparison group) will be needed to be able to detect the hypothesized difference of 10 MDI points (= 0.67 SD) between the experimental and control condition with 5% level of significance and 90% power [50,51]. Assuming 10% attrition per year and possible missing values, at least 60 children per condition and group, or at least 120 children with birth asphyxia and 120 healthy comparison children for a total of 240, need to be enrolled and randomized to either EDI plus HSC or HSC alone to achieve the desired power.

Consequently, at least 80 children (40 in each group) were to be enrolled in each country. However, due to anticipated higher attrition in the healthy comparison group, the sites were to enroll additional children from this group. In total, 431 children across the two groups have been enrolled and randomized during the defined enrollment period, including 174 in the birth asphyxia and 257 in the healthy comparison group.

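### The 36-month MDI comparison is specified as an unadjusted t-test without a site term, and the plan does not say whether this test or the added GEE and hierarchical models decide the primary hypothesis

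*Protocol article*

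**What the plan says.** All references are to the protocol article.

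- **Named test (Data analysis).** "Comparisons of MDI between the two trial conditions at the end of the study will employ student's t-test", repeated for the asphyxia and comparison groups. No site, covariate or trainer term is attached.
- **Further models (Data analysis).** The next lines add that "generalizing estimating equations models and hierarchical linear modeling will be used to perform the analysis on the primary and secondary outcome variables". They give no clustering unit or covariates, and no ranking against the t-test.
- **Allocation (Randomization).** Lists were produced separately for infants with and without asphyxia, in blocks of 4 or 8. "Each site was provided with sealed envelopes with the randomization assignment". Stratification by site is not stated in words.
- **Enrolment by country (Power analysis).** "at least 80 children (40 in each group) were to be enrolled in each country".
- **Trainers (Staff, training, and implementation).** "Each parent-child pair has an assigned trainer conducting the home visits". The number of trainers and their caseload are not given. The Design section says that trainers know which condition they are in; it does not say that each works in only one.
- **Enrolment data (Measures for testing hypotheses).** The parent attitude and knowledge inventory and "a family demographics and resources measures were administered at enrollment prior to neonatal age 2 weeks". MDI is first measured at 12 months, so there is no baseline MDI.

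**The concern.** The t-test is the only comparison of the primary outcome that the article spells out, and it treats the children in each group as one homogeneous, independent sample. Two features of the design sit badly with that.

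First, allocation was blocked from envelopes held at each site, in three countries. The Bayley scales are given in local languages, with some cultural adaptation, in settings where the article says they are not in routine use. Differences in mean MDI between countries are plausible. Blocking within site would balance those differences between arms, but a t-test still counts them as error, which costs precision.

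Second, one trainer visits a family every two weeks for three years, and a trainer presumably serves several families. If trainers belong to one arm, outcomes within a trainer may be correlated, and a t-test would understate the uncertainty.

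A separate difficulty is that two kinds of analysis are named for one primary outcome. If the t-test and a hierarchical model disagree, nothing in the article says which one answers the primary hypothesis.

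**Working it through.** **Inputs from the article.** Difference 10 MDI points = 0.67 SD, so SD = 15. Significance 5%, power 90%, 40 completers per condition and group, attrition 10% per year, 174 infants with asphyxia and 257 comparison infants enrolled.

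**Assumptions (not in the article).** Site share of MDI variance 5-20%; trainer ICC 0.02-0.05; 4-10 children per trainer within one group; two-sided testing; 1:1 allocation.

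**1. The plan's own figure.** n per arm = 2(15/10)²(z_α + z_β)².
- One-sided: 4.5 × (1.645 + 1.282)² = 38.5, so 39 (40 by noncentral t). This reproduces the stated 40.
- Two-sided: 4.5 × (1.960 + 1.282)² = 47.3, so 48 (49 by noncentral t). Two-sided power at 40 per arm is 83.8% (t).

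The calculation treats children as independent and has no site or trainer term. The unstated sidedness is a separate matter; two-sided figures are used below.

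**2. Likely completers.** 174 × 0.9³ = 126.8, or about 63 per arm in the asphyxia group.

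**3. Site left in the error term.** With site share ρ and balance within site, the t-test standard error is too large by 1/√(1−ρ), and its true type I error is 2·P(Z > 1.96/√(1−ρ)). Adjusted power uses SD = 15√(1−ρ).

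| ρ | SE ratio | True type I error | Power with site fitted, 40 per arm | Same, 63 per arm |
|---|---|---|---|---|
| 0.05 | 1.026 | 4.4% | 85.5% | 96.8% |
| 0.20 | 1.118 | 2.8% | 90.8% | 98.6% |

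Unadjusted power at SD 15 is 83.8% at 40 per arm and 96.0% at 63. The gain is about 2 to 7 points at the planned size and 1 to 3 points at the likely size.

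Simulation (3 sites, 14 per arm per site, no trainer effect, 6,000 runs for type I error and 3,000 for power) puts the gap lower, because balance within site already helps the t-test. With ρ = 0.20, power was 89.5% for the t-test and 92.7% with site fitted, and t-test type I error was 3.3%.

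**4. Trainers, if nested within arm.** Design effect DE = 1 + (m−1)·ICC; type I error of a nominal 5% test = 2·P(Z > 1.96/√DE).

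| m per trainer within group | ICC | DE | True type I error | 63 counts as |
|---|---|---|---|---|
| 4 | 0.02 | 1.06 | 5.7% | 59 |
| 4 | 0.05 | 1.15 | 6.8% | 55 |
| 10 | 0.02 | 1.18 | 7.1% | 53 |
| 10 | 0.05 | 1.45 | 10.4% | 43 |

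The row m = 4 matters because the t-test is run within each group. Asphyxia infants are 174/431 = 40% of those enrolled, so a caseload of 10 spread over both groups gives about 4 per trainer in the asphyxia comparison.

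**5. Both features together (simulation, ρ = 0.10, ICC 0.05).**
- Trainers nested in arm, 7 children each: type I error 7.9% for the t-test, 9.2% with site alone fitted.
- Trainers serving both arms: 4.0% for the t-test, 4.6% with site fitted.

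So the net direction depends on trainer allocation. If trainers are nested, fitting site alone removes the conservatism that partly offsets the trainer effect.

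**The case against.** The strongest reply is that the same section plans GEE and hierarchical models on the primary outcome. Both can handle correlated data, and their clustering units and covariates are details that an article may leave to the full protocol or analysis plan. That stands: their absence here is not a fault, and the plan does not ignore correlation altogether. It does not settle the point, because those models come as additions and the article does not say which analysis decides. Nor does the article label the t-test as primary; that is an inference from its match to the primary hypothesis.

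Four stronger readings are tempting, and the document does not support them.

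- **The primary p-value and interval are wrong.** Omitting site makes the standard error too large; omitting trainers nested in arm makes it too small. Which prevails depends on an ICC, a caseload and a trainer allocation that are not given. With respect to site alone, the t-test is valid but conservative.
- **False positives are inflated.** This requires trainers who work in one arm. The text leans that way but does not say so, and with trainers in both arms the simulation shows no inflation.
- **Baseline data go unused.** Child, parent and family characteristics are planned as moderators. They are absent only from the t-test.
- **The trial is short of power because site is omitted.** At about 63 completers per arm, two-sided power is already about 96%. Even the worst clustering case above leaves an effective 43 per arm, more than the plan's own 40.

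**Conclusion.** The point holds as a matter of precision and clarity. The article fixes an unadjusted t-test for the primary outcome although envelopes were held by site and enrolment measures are available, and it leaves the deciding analysis open.

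For site, the cost is a standard error 3-12% too large. That is up to about 7 points of power at 40 per condition, and 1 to 3 points at the size likely to be reached. It rests on an assumed 5-20% site share and on implied stratification. Confidence is good in the direction of this effect and lower in its size.

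For trainers, the concern is conditional: type I error of about 6-10% if they are nested in arm with an ICC of 0.02-0.05 and 4-10 children each, and no inflation if they serve both arms. The change is worth making, but nothing here invalidates the trial.

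**What to change.** Before outcomes are unblinded, name one primary analysis for each group: a linear model of 36-month MDI on condition, with site or country as a fixed effect and a few prespecified enrolment covariates, for example birth weight, maternal education and family resources. Keep the unadjusted t-test as a supportive analysis, and state the role of the GEE and hierarchical models.

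State whether each trainer works in one arm or both, and how many children each serves within a group. If trainers work in one arm only, add a trainer random effect or a cluster-robust standard error with a small-sample correction, at least as a sensitivity analysis. Under nesting, site adjustment should not be reported without it.

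The cost is wording. Site, birth weight, family measures and assigned trainer are already part of the trial's procedures. The trainer term may widen the interval, and the covariate gain may be modest because there is no baseline MDI.

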## Discussion

### Administrative structures - Trial Steering Committee

The Trial Steering Committee (TSC) consists of all principal investigators and the supervising trial manager. Statisticians and field investigators join the TSC deliberations as needed. The TSC met initially to finalize the protocol and organization of the trial. The TSC then meets regularly to discuss issues such as recruitment progress, trial implementation data, and indications of protocol deviations. The TSC evaluates this information and take action accordingly. It also plans the training of parent trainers and evaluators.

### Research ethics

The study was reviewed and approved by the Institutional Review Boards (IRBs) at all participating sites in India, Pakistan, and Zambia, as well as at the central U.S. sites at the University of Alabama at Birmingham and the Research Triangle Institute (RTI). The study has been reviewed and approved also by the NICHD Global Network for Women's and Children's Health Research data monitoring committee (DMC). The primary publication for the trial will follow CONSORT guidelines for randomized controlled trials. Criteria for authorship of all papers, presentations, and reports resulting from the study will conform to ICMJE standards.

### Data and process monitoring

Adverse events for the trial, including the death of a child or mother or hospitalization of the child, are reported to the DMC. Reports and recommendations from the DMC are distributed to the IRBs and the project officer representing the funding agency (NICHD). Process monitoring and management is directed by the international site investigators and includes: (1) assuring high compliance rates with the intervention visits (>80%); (2) evaluating accuracy and completeness of data collected, entered, and transmitted (jointly with the DCC); (3) assuring that all personnel are fulfilling their obligations; (4) addressing ad hoc problems and maintaining communication; and (5) maintaining proper IRB approval. The DCC also assures inter-site consistency. Data on knowledge are collected before and immediately after each staff training session. Parent trainer competency is observed and evaluated with a checklist by a supervisor at one home visit per six months.

### Implications

Birth asphyxia (defined as inability of a neonate to establish spontaneous breathing after birth) is a major cause of long-term neurodevelopmental morbidity, such as intellectual disability and cerebral palsy, and affects a disproportionate number of children in L/LMIC. EDI has shown in numerous prior RCTs in L/LMIC to be capable of preventing or limiting the declines in cognitive development that may occur in the early years of life in children following brain insult or who are otherwise at risk for developmental problems. The findings from the current RCT therefore have the potential to identify strategies for reducing neurodevelopmental disabilities in at-risk young children in L/LMIC that require relatively low resources.

## Abbreviations

ASQ: Ages & Stages Questionnaire; ASQ: SE Ages & Stages Questionnaire: Social-Emotional; BRAIN-HIT: Brain Research to Ameliorate Impaired Neurodevelopment - Home-based Intervention Trial; BSID: Bayley Scales of Infant Development; CONSORT: Consolidated Standards of Reporting Trials; DALY: Disability-Adjusted Life Year; DCC: Data Coordination Center; DMC: Data Monitoring Committee; EDI: Early Developmental Intervention; FB FIRST BREATH: HSC Health and Safety Counseling; ICMJE: International Committee of Medical Journal Editors; IRB: Institutional Review Board; L/LMIC: Low and Low-Middle Income Countries; MDI: Mental Development Index; NICHD: National Institute of Child Health and Human Development; NIH: National Institutes of Health; PDI: Physical Development Index; RCT: Randomized Controlled trial; TSC: Trial Steering Committee.
